#### Family Adherence to the TMexD

Adherence to the TMexD will be estimated with a list of 15 groups of typical Mexican foods proposed by Valerino-Perea et al [53]. A score is assigned to each food, summing the corresponding points if the food was consumed and no points (0) if not consumed, with 21 points being the highest possible score. This instrument was originally developed in Spanish and specifically designed for the Mexican population, applied in national survey data (Encuesta Nacional de Salud y Nutrición).

### Design of the ESCOLARISANO Program Curriculum

The curriculum was based on social cognitive theory (SCT), the behavior change wheel (BCW) with the COM-B theoretical framework (capability, opportunity, and motivation influencing behavior), and the transtheoretical theory (TTT), which have been used in public health programs for disease prevention and health promotion [54-56]. Program content includes recommendations from official health and childhood institutions [57] for the prevention of malnutrition, food insecurity, and cardiometabolic diseases [58]. Nutrition education and cooking workshops, adapted to the regional, cultural, and social context of participants, will be delivered in two 1-hour weekly sessions. One additional 1-hour weekly PA session will reinforce the official Ministry of Education PA curriculum. A conceptual model, shown in Figure 2 was proposed to explain the intervention and the relationship among its components, the thematic content, and the variables involved. The operationalization of study constructs through intervention components is detailed in Table 1. The intervention will be implemented over 4 months, covering the topics and activities outlined in Table 2.

**Figure 2. F2:**
[figure not shown]
Conceptual model for the ESCOLARISANO randomized controlled trial. COM-B: capability, opportunity, and motivation influencing behavior; SES: socioeconomic status.

**Table 1. T1:** Operationalization of study constructs through intervention components.

COM-B^a^ components and SCT^b^ constructs	TTM^c^ stages targeted	Behavior change mechanisms	Intervention components
Psychological capability			
Behavioral capability	Precontemplation → contemplation	Increased knowledge and practical skills required to perform the behavior.	Nutrition education: educational sessions on healthy eating, food label reading, water consumption, and the role of breakfast.
Observational learning	Contemplation → preparation	Learning through positive role models.	Guided demonstrations (healthy lunchbox preparation), visual examples, and group-based activities.
Outcome expectations	Contemplation	Cognitive restructuring regarding short- and long-term benefits.	Guided discussions on the health benefits of healthy eating, physical activity, and sleep.
Self-regulation (emotional regulation)	Preparation → action	Emotion identification and regulation.	Emotion awareness: learning to recognize emotions, applying emotion regulation strategies, and addressing body shaming.
Physical capability			
Behavioral capability	Action	Development of physical skills to perform the behavior.	Physical activity promotion: guided and supervised physical activity practice.
Reflective motivation			
Self-regulation	Preparation → action	Planning, monitoring, and adjustment of behavior; integration of multiple healthy behaviors.	Goal setting, habit tracking, follow-up, and feedback.
Self-efficacy	Preparation	Increased perceived confidence to engage in the behavior.	Achievable goal setting and feedback.
Outcome expectations	Action → maintenance	Conscious evaluation of behavioral consequences.	Guided reflection on perceived changes in well-being and energy levels.
Automatic motivation			
Reinforcement	Action → maintenance	Habit strengthening through positive reinforcement.	Verbal recognition, feedback, and social reinforcement.
Social opportunity			
Observational learning	All stages	Social normalization of healthy behaviors.	Group activities and participatory dynamics.

a COM-B: capability, opportunity, and motivation influencing behavior.

b SCT: social cognitive theory.

c TTM: transtheoretical model.

**Table 2. T2:** Thematic content of the intervention.

Phases	Description	Instruments/Indicators/Activities
0. Staff training and recruitment	Staff training on techniques and methodologies for anthropometric and dietary assessment, etc. Preparation and standardization of tools, instruments, materials, questionnaires, and data recording sheets. Recruitment logistics and curriculum design.	Advertising campaign for the intervention. Printing of questionnaires and/or paper formats. Practical rehearsal for staff, specifically on anthropometry and completing questionnaires and/or instruments.
1. Baseline measurements	Baseline measurements.	Application of baseline questionnaires and recalls: informed consent, family medical history, anthropometrics, blood pressure, knowledge, body image perception, family interaction (APGAR)^a^, psychosocial well-being (SDQ^b^), adherence to the traditional Mexican diet, 24h-R^c^, sleep time, and quality.
2. Intervention curriculum	Topics: promotion of a healthy lifestyle, physical exercise, health education, child nutrition and health, emotions and mental health, personal hygiene, cooking workshops, prevention of cardiometabolic diseases (overweight, obesity, diabetes, and hypertension).	Activities: putting on a t-shirt; healthy eating; exercising, getting active, and moving one’s body; recognizing one’s emotions and mental health; preparing a healthy lunch; sip by sip; cleansing, loving and taking care of one’s body; reducing screen time; bedtime habits; healthy breakfast; reading nutrition labels; cooking workshop 1: preparing fruit salad with yogurt, cooking workshop 2: preparing refreshing drinks, cooking workshop 3: preparing banana popsicles with peanut butter; comprehensive healthy living.
3. Final measurements (immediately after intervention)	Measurements. Data analysis: data capture, review, cleaning, and modeling.	Anthropometrics and blood pressure. Questionnaires and recalls (same as baseline). Assessment of intervention indicators: effectiveness, retention, motivation to change, viability, fidelity, feasibility, and acceptability. Data analysis using SPSS software.
4. Final measurements (6 months postintervention)	Measurements. Data analysis: data capture, review, cleaning, and modeling.	Anthropometrics and blood pressure. Questionnaires and recalls (same as baseline). Data analysis using SPSS software.

a Family APGAR (Adaptability, Partnership, Growth, Affection, and Resolve): a questionnaire used to assess family functioning and the level of satisfaction family members have with their relationships.

b SDQ: Strengths and Difficulties Questionnaire.

c 24h-R: 24-hour recall.

Participants will be encouraged to engage in a variety of free PA activities at school and home [19]. Among the activities are walks, runs, ball games, etc. It is crucial to include this diversity of topics and activities because it is a multidisciplinary program characterized by addressing the problem comprehensively. Participant attendance will be recorded, and evidence of the activities for each topic will be kept. Communication with teachers and parents or guardians via WhatsApp and in person at schools will be available at all times to address questions regarding the research, children’s progress, behavior, and diagnoses or findings.

### Behavioral Indicators (Before and After the Intervention)

#### 24-Hour Recall

Food intake will be assessed preintervention and postintervention in children in grades 4 to 6 using 2 nonconsecutive 24-hour recalls (24h-R), with the United States Department of Agriculture Automated Multiple-Pass Method [59]. The procedure consists of conducting an individual interview by a dietitian staff member and recording, on paper, the participant’s total food consumption during the day prior to the interview (from the time the individual woke up until the time they went to bed), ensuring that all foods and beverages are included. During the interview, key questions will be asked to stimulate the participants’ memory. To estimate the participant’s daily nutrient intake, recalls will be processed on the ASA24 site by the dietitian staff member, and for dishes not listed on the ASA24 platform, the ingredients will be individually itemized and recorded on the website.

#### Indicators of Diet Quality

The following dietary quality indicators will be estimated to examine their association with cardiometabolic risk factors at baseline and to assess changes in eating behaviors after the intervention.

##### Healthy Eating Index

The Healthy Eating Index (HEI) 2024 will be estimated [60]. The overall HEI score will be calculated using the following classification: (1) optimal, with an HEI score greater than or equal to 81; (2) requires improvement, with an HEI score between 51 and 80; (3) poor, with an HEI score less than or equal to 50 [61].

##### NOVA System

The classification of foods by NOVA groups will be carried out into the following categories: NOVA 1: nonperishable or minimally processed foods; NOVA 2: processed culinary ingredients; NOVA 3: processed foods; NOVA 4: ultra-processed foods (UPFs) [62].

##### Dietary Components Related to Cardiometabolic Risk

Dietary components related to cardiometabolic risk include daily consumption of risky dietary components, such as total and added sugars, sodium, and saturated fat, among others.

### Physical Activity

The 3-day physical activity recall assesses the time spent on different types of activities rated as light, moderate, intense, or very intense, recorded in periods of 30 minutes from when the interviewee got up in the morning until they went to sleep. Activities are assigned a metabolic equivalent of task (MET) level (moderate-to-vigorous physical activity ≥3 METs; vigorous physical activity ≥6 METs), and the summary scores are tallied as total METs per day [63]. This questionnaire has been validated in Latin American children and adolescents [64] and will be administered to participants from grades 4 to 6 [65].

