The present intervention protocol addresses childhood obesity in an integrative and unconventional manner, generating multifactorial knowledge about family behavior, individual factors, and the school environment. The aim of this protocol is to measure the effect of an intervention designed for low-income Mexican schoolchildren, focused on promoting healthy lifestyles for the prevention of obesity and cardiometabolic diseases. Specific aim 1 is to analyze whether baseline anthropometric and behavioral variables are associated with psychosocial well-being, family interaction or functionality, and perceptions of childhood obesity in the home environment. Specific aim 2 is to evaluate the effectiveness of the intervention in terms of retention, motivation to change, fidelity, and acceptability of the program by schoolchildren. Specific aim 3 focuses on evaluating changes in health behaviors at the end of the intervention and after 6 months in knowledge, diet quality, exercise time, and sleep time and quality.

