### Statistical Analysis

The normal distribution of the data will be verified using skewness, kurtosis, and Kolmogorov-Smirnov tests. Quantitative data with nonnormal distribution will be mathematically transformed for parametric analysis, or alternatively, nonparametric analysis will be used. Means and SDs will be calculated for continuous variables and percentages for categorical variables. To test age, sex, socioeconomic status, and location baseline differences, we will use chi-square tests for qualitative demographic variables (eg, socioeconomic level, family medical history, sport practice, etc) and analysis of covariance for quantitative variables (eg, anthropometrics, dietary intakes, HEI, TMexD, sleep time, BIP, family interaction, and psychosocial well-being). To evaluate specific aim 1, potential baseline associations of dependent variables (eg, anthropometrics and blood pressure) with independent behavioral variables (eg, dietary intakes, exercise and sleep time, family interaction, psychosocial well-being, and perception of childhood obesity) will be tested using multiple linear regression, starting with univariate regression (*P*<.2 and biological plausibility). Models will be built by a combination of univariate analysis and forward stepwise model selection using *P*≤.05 and biological plausibility. Preliminary models will be assessed for possible interactions (*P*≤.1) between sex and other variables included in the model, for collinearity (variance inflation factor<10), and for linear regression assumptions (linearity, normality, and homoscedasticity) using residual plots. Specific aim 2 will use mixed methods (qualitative and quantitative) to analyze results in terms of retention, fidelity, and acceptability of the intervention by children and school administrators. Specific aim 3 will compare the changes between the experimental arms (intervention vs control) from baseline to postintervention and to the 6-month follow-up in anthropometrics, blood pressure, HEI, dietary intakes, PA, sleep time, and knowledge. Primary analyses will follow the intention-to-treat principle. Given the hierarchical structure of the data (students nested within classrooms and classrooms within schools) and the repeated measurements over time (baseline, postintervention, and 6-month follow-up), intervention effects will be evaluated using multilevel mixed-effects regression models. Due to the cluster-based allocation, the intraclass correlation will be considered, potential attrition will be monitored, and all analyses will account for clustering to provide valid inferences. Models will include fixed effects for study arm, time, and the arm×time interaction, and random effects for classroom and school to account for intracluster correlation. Baseline values of the outcomes and covariates will be included as appropriate. Effect estimates with 95% CIs will be reported. We will examine model assumptions and fit indices. SPSS (IBM SPSS Statistics version 21.0) and STATA (StataCorp version 14.0) software will be used, with a *P* value <.05 for all statistical analyses.

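### The only stated physical activity score, total METs per day over waking blocks, depends on hours awake and does not measure the exercise time named in specific aim 3

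*Protocol article*

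**What the plan says.** The Physical Activity section of the protocol article describes a 3-day recall, "recorded in periods of 30 minutes from when the interviewee got up in the morning until they went to sleep". Each activity receives a MET level, two cut-offs are given ("moderate-to-vigorous physical activity ≥3 METs; vigorous physical activity ≥6 METs"), and then "the summary scores are tallied as total METs per day". No other summary score is stated. The recall "will be administered to participants from grades 4 to 6".

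Specific aim 3, at the end of the Introduction, evaluates changes in "knowledge, diet quality, exercise time, and sleep time and quality". The Statistical Analysis section lists the outcomes compared between arms as "anthropometrics, blood pressure, HEI, dietary intakes, PA, sleep time, and knowledge". It does not say which activity variable enters the model, and it mentions no adjustment for waking time.

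Sleep is part of the intervention. The curriculum row of Table 2 includes "reducing screen time; bedtime habits", and Table 1 includes discussion of the benefits of sleep. The curriculum section adds one 1-hour physical activity session per week in the intervention arm.

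**The concern.** A total summed over waking blocks is driven partly by how long the child is awake. A block spent sitting still adds its MET value, while a block spent asleep is outside the recording window and adds nothing. Two children with the same exercise time but different bedtimes therefore get different scores.

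This matters because activity and sleep are both addressed by the program and both compared between arms. If sleep lengthens more under the intervention, that arm loses waking blocks. Neither randomization nor the mixed model removes the resulting shift, because it is a consequence of the intervention acting through the scoring rule. An actual gain in exercise could then look small, absent or negative.

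Even without any sleep effect, total METs is not a measure of exercise time. The aim is stated in time, and the Introduction cites its activity recommendation in minutes per day.

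**Working it through.** The article states no expected activity effect, so there is no figure to reproduce. The check applies the stated scoring rule.

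**Inputs from the article:** 30-minute blocks over waking time only; score equal to the sum of METs; one extra 1-hour session per week, which is 60/7 = 8.6 min/day.

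**Assumptions, not in the article:** sedentary time s = 1.5 METs (range 1.3 to 2.0); exercise x = 4 METs (range 3 to 6); extra exercise and extra sleep both replace sedentary waking time.

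**Formula.** With an exercise gain E and a sleep gain S in min/day:

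- change in score = [E(x − s) − S·s] / 30
- sleep gain that cancels the exercise gain = E(x − s) / s

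**Results with s = 1.5 and x = 4:**

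| Exercise gain (min/day) | No extra sleep | +15 min | +30 min | +60 min | Cancelled at |
|---|---|---|---|---|---|
| 30 | +2.5 | +1.75 | +1.0 | −0.5 | 30 × 2.5/1.5 = 50 min |
| 8.6 | +0.71 | −0.04 | −0.79 | −2.29 | 8.57 × 2.5/1.5 = 14.3 min |

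**The same as a whole day.** Assume 30 waking blocks, 26 sedentary and 4 of exercise.

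- Before: 26 × 1.5 + 4 × 4 = 55.
- One more exercise block, sleep unchanged: 25 × 1.5 + 5 × 4 = 57.5.
- One more exercise block, 30 minutes more sleep: 24 × 1.5 + 5 × 4 = 56.
- One more exercise block, 60 minutes more sleep: 23 × 1.5 + 5 × 4 = 54.5.

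Time at 3 METs or more rises from 120 to 150 minutes in all three later cases.

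**Range over the assumed MET values.**

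- Cancelling the 8.6 min/day gain takes from 4.3 min of sleep (s = 2.0, x = 3: 8.57 × 1/2) to 31.0 min (s = 1.3, x = 6: 8.57 × 4.7/1.3).
- Cancelling the 30 min/day gain takes from 15 min (30 × 1/2) to 108 min (30 × 4.7/1.3).

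**If sleep were scored after all.** At about 0.95 MET for sleep, contrary to the stated window, each minute of extra sleep costs s − 0.95. The 8.6 min/day gain is then cancelled at 8.57 × 2.5/0.55 = 39 min in the base case (range 8.2 to 115). The problem shrinks but remains.

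**Does dividing by waking time help?** Take the 55-MET day, add 60 minutes of sleep and leave exercise unchanged. Mean METs per waking block goes from 55/30 = 1.83 to 52/28 = 1.86. That score would show an activity gain that did not occur.

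**The case against.** The section describes how an instrument is scored and never names total METs as the aim 3 outcome. It opens by saying that the recall assesses time by intensity, it gives the 3 and 6 MET cut-offs, and it speaks of summary scores in the plural. METs might be summed within those categories, which would largely remove the dependence on sleep. The article is also a condensed document, and the choice of derived variable is often left to the analysis plan.

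This has weight: a fuller plan may well use time above the cut-offs. But the article does state a summary, it states only one, and that one does not match the aim. METs summed within categories would still not be exercise time.

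The other side is also right on several limits. A reader might infer that the program sets out to lengthen sleep and will therefore bias the activity result toward harm. The documents do not support that. They name sleep hygiene, bedtime habits and sleep time as an outcome, but no goal of longer sleep and no expected gain; better sleep quality alone would leave waking time as it was. That sitting is scored in every waking block is inferred from the recording window, since no MET value for sitting is given. With a 30 min/day exercise gain, reversal needs more than 50 minutes of extra sleep in the base case, and at 60 minutes the score falls by only 0.5 out of 55. Sleep time is analysed too, so a sleep gain would be visible to whoever interprets the result.

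**Conclusion.** The mismatch between the stated score and the stated aim holds on the text alone. The distortion through sleep is conditional: it requires sleep to lengthen more in the intervention arm, at the expense of sedentary waking time. Under the base-case MET values, 30 minutes more sleep removes 60% of the apparent effect of a 30 min/day exercise gain (1.5 of 2.5). About 14 minutes removes all of the effect of the protocol's own added session, if that session is the only gain. These sizes rest on assumed values, with the ranges shown above. The issue affects one self-reported outcome among several, in grades 4 to 6 only. It should be corrected because the sign of that outcome's effect can depend on sleep rather than on exercise.

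**What to change.** Name the aim 3 activity outcome as minutes per day in blocks of at least 3 METs, with blocks of at least 6 METs as the vigorous part. Both cut-offs are already in the Physical Activity section. This measure does not change with sleep as long as the extra sleep replaces sedentary time.

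Keep total METs per day as a secondary, descriptive score, read alongside the sleep-time result. Do not substitute mean METs per waking hour, which rises with longer sleep even when exercise is unchanged.

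No new data are needed, because the existing recall forms can be re-scored. The cost is in transparency. Table 3 shows all measurements complete and data analysis marked done for two of the four schools, with interpretation open for all four. The change must therefore be dated and reported as made after data collection, with total METs reported too. If a fuller plan already specified time above the cut-offs before the data were seen, citing it would be enough.

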### Sleep Hygiene

Sleep time and quality will be assessed using the 24-hour sleep questionnaire applied on 3 different days. The questionnaire consists of 12 questions covering the start and end of sleep (bedtime, waking time, and getting-up time), sleep characteristics (latency, number of sleep interruptions, sleep duration), subjective perception (how you felt upon waking, sleep quality), and comparison with usual habits (perceived amount of sleep). Information is collected using the ASA24 sleep module [66].

### Intervention Indicators

#### Preintervention Feasibility and Viability

The feasibility and viability assessment will be carried out prior to the intervention using checklists. We will assess whether the proposal is feasible in the specific context of the school, adapting the program to the conditions of each school, and meeting technical, economic, and human resource requirements based on the number of participants per school.

#### Assessment of Knowledge and Motivation for Change

Acquired knowledge, motivation for change, and satisfaction will be evaluated through a pretest and posttest. For motivation and willingness to change behavior [67], confidence and the importance attributed to the change are analyzed through 2 questions: “What level of confidence do you feel in being able to make this change?” on a scale of 1 (zero confidence) to 10 (extreme confidence); and “How important is it for you to make this change?” where 1 indicates little importance and 10 indicates the utmost importance [68].

#### Effectiveness

Results obtained in the experimental arm will be compared with those of the control arm to analyze the significant differences in behavioral and health outcomes between them. This comparison will provide a more robust perspective on the real impact of the intervention on the habits and health of the participants [69].

